## Methods

### Trial Design

This is a double-blind, randomized controlled intervention trial of healthy male and female term infants. Briefly, the trial will include three parallel arms: (1) the EG that will consume the interventional product (ready-to-feed infant formula containing 2 HMOs), (2) the CG that will consume the comparator product (CP, ready-to-feed infant formula without the 2 HMOs), and a BG as reference. The study constitutes of an intervention period (age 0-6 months) where infants from both the CG and EG will be exposed to either the interventional product or CP to evaluate their effects on key study outcomes, followed by an observational follow-up period (age 6-12 months) to evaluate long term postintervention effects of interventional product and CP on gut microbiome maturation and later incidence of illnesses, infections as well as immune status (Figure 1). The trial will include 5 scheduled clinic visits (V1: infant age 3-14 days, V2: infant age 3 months, V3: infant age 6 months, V4: infant age 9 months, and V5: infant age 12 months). Phone call appointments will serve as reminder calls for the collection of stool samples and completion of relevant questionnaires that need to be completed as part of the home procedures before the clinic visits. A brief overview of the study sessions and procedures is summarized in Table 1 and described in detail.

**Figure 1 figure1:**
[figure not shown]
Graphical representation of the 3-arm study design. Randomization is for the formula-fed group only. 2’FL: 2-fucosyllactose; BG: breastfed group; CG: control group; EG: experimental group; HMO: human milk oligosaccharide; LNnT: lacto-N-neotetraose; RTF: ready-to-feed; V: visit.

**Table 1 table1:** Study sessions and procedure.

Procedures			Intervention period													Observation period						
			V1^a^		H1^b^		H2		V2		H3		V3		H4			V4		H5		V5
Informed consent			✓																			
Inclusion and exclusion criteria			✓																			
Physical examination			✓																			✓
Medical history			✓																			
Demographics			✓																			
Anthropometry			✓						✓				✓					✓				✓
Randomization			✓																			
Fecal samples					✓		✓				✓				✓					✓		
**Questionnaires**																						
	IGSQ-13^c^	✓						✓				✓										
	PISI^d^							✓				✓					✓				✓	
	BISQ^e^	✓						✓				✓										
	ITQoL-SF^f^ 47							✓				✓										
**Diaries**																						
	Stooling	✓				✓				✓												
	3-day food									✓				✓					✓			
	Breastfeeding (BG^g^ only)	✓						✓				✓					✓				✓	
	Formula milk intake	✓						✓				✓					✓				✓	
	Infant illness	✓		✓		✓		✓		✓		✓		✓			✓		✓		✓	
**Investigational product**																						
	Administer trial formula (EG^h^/CG^i^ only)			✓		✓		✓		✓		✓										
	Adverse event collection	✓		✓		✓		✓		✓		✓		✓			✓		✓		✓	

^a^V: visit.

^b^H: home.

^c^IGSQ: Infant Gastrointestinal Symptom Questionnaire.

^d^PISI: Pediatric Immune System Index.

^e^BISQ: Brief Infant Sleep Questionnaire.

^f^ITQoL-SF: Infant Toddler Quality of Life Questionnaire-Short Form.

^g^BG: breastfed group.

^h^EG: experimental group.

^i^CG: control group.

### Trial Population and Eligibility Criteria

The trial population will consist of healthy infants aged 3-14 days at enrollment. Potential participants will be referred by the clinical care team to the investigator to check whether they meet the eligibility criteria, and the investigator will provide a thorough explanation of the trial. The eligibility of the potential participant will be confirmed according to the inclusion and exclusion criteria (Textbox 1), and each participant will be assigned a unique identification number.

Inclusion and exclusion criteria.
**Inclusion criteria**
Singleton, healthy, full-term gestational birth (≥37 completed weeks of gestation), with a birth weight ≥2.5 kg and ≤4.5 kg and postnatal age of 3-14 days (date of birth=day 0), inclusive.Willing and able to comply with scheduled visits and the requirements of this trial protocol.Access to a working freezer.For the formula-fed groups: infant is exclusively consuming and tolerating a cow’s milk infant formula for at least 3 days before enrollment. The infant’s mother has independently elected not to breastfeed.For the breastfed reference group: the infant has been exclusively consuming breastmilk since birth, and the infant’s mother has decided to continue until at least age 3 months.
**Exclusion criteria**
Infants receiving complementary foods or liquids, defined as 4 or more teaspoons per day or approximately 20 g per day of complementary foods or liquids at or before enrollment.Infants who have a medical condition or history that could increase the risk associated with trial participation or interfere with the interpretation of trial results.Infants who are presently receiving or have received before enrollment probiotic supplements or medications or supplements known or suspected to affect fat digestion, absorption, or metabolism (eg, pancreatic enzymes); stool characteristics or microbiome (eg, oral and systemic antibiotics, glycerin suppositories, bismuth-containing medications, docusate, Maltsupex, or lactulose); growth (eg, insulin or growth hormone); or gastric acid secretion.Infants currently participating or having participated in another clinical trial since birth.Infants with a known or suspected cow’s milk protein intolerance or allergy, lactose intolerance, soy intolerance, or allergy.

### Study Sites and Recruitment

Infants for this trial will be recruited from the following sites in China, including Xinhua Hospital affiliated to Shanghai Jiao Tong University School of Medicine, The International Peace Maternity & Child Health Hospital of China Welfare Institute at Shanghai, Shanghai First Maternal, Infant Hospital and Nanjing Women and Children Healthcare Center, and Peking University Third Hospital. The leading site is Xinhua Hospital affiliated to Shanghai Jiao Tong University School of Medicine, which is one of the top Pediatric Research centers in China specialized and well recognized in pediatric education, health care and research, while all the other participating hospitals are among the top women-and-children’s health care hospitals, providing comprehensive health care in the north east and middle east regions of China.

At recruitment, the infants’ parents or legally authorized representative (LAR) should have already made the decision regarding the feeding choice for their infant, and only when the parents have independently decided to formula-feed their infant, the infant will be enrolled into the clinical trial. No public or commercial advertisements of the trial, including research labels or product brand names, will be used. The benefits of breastfeeding will be discussed with all parents. Breastfeeding support via appointment with a qualified lactation consultant will be provided, before enrollment, to both the breast-fed and formula-fed groups, to ensure parents have received the appropriate advice. During the study, there will be dedicated investigational staff keeping close contact with the participants to acquire knowledge of any untoward medical event of their infants, and to remind them of study-related procedures such as stool sample collection and questionnaire completion.

### Randomization Procedure and Blinding

Participants will be assigned to the EG or CG groups randomly using Medidata Randomization Trial Supply Management with the dynamic allocation algorithm at the first visit. An allocation ratio of 1:1 stratified by site, sex (female or male), and mode of delivery (cesarean section [CS] or vaginal) will be carried out. Neither the investigator or site team nor the participant will know which investigational product each participant is receiving until after database lock. Considering the double-blinded nature of the trial, the identity of the specific product will be blinded to participants, participants’ parents, or caregivers (if applicable), support staff, investigators, site team, contract research organization managing the trial (except specified delegated regulatory staff), and study sponsors (except the manufacturing site, supply, and quality managers). The products will be identical in packaging, color, and taste. They will be packaged and labeled identically but will have distinguishable product codes printed on the packaging. Unblinding will be done only in case of emergency or after database lock for final statistical analyses.

### Intervention

The EG will receive a ready-to-feed, liquid, bovine milk–based whey, predominant term formula supplemented with 1 g/L 2-fucosyllactose and 0.45 g/L lacto-N-neotetraose. The dosage of the HMO blend used in the trial is well within the range of HMO concentrations found in mature breast milk [32,33]. The formula contains 67 kcal/100 mL, 2 g protein/100 kcal (65% whey/35% casein), 10.6 g carbohydrates/100 kcal, and 5.4 g lipids/100 kcal. The CG will receive the same formula but without the HMOs. Both formulas are enriched with an advanced whey protein profile obtained using a unique whey protein ingredient that delivers a formula enriched in α-lactalbumin, osteopontin, lactoferrin, and milk-fat-globule membrane (MFGM) proteins and lipids (α-MFGM) [34] and a casein profile comprised of A2 β-Casein, in combination with an Sn-2 palmitate enriched triacylglycerol core and contain vitamins and minerals in amounts intended for full nutritional support of infants from birth to 6 months. Formulas will be started after the baseline stool sample collection on study day 1 or 2 and continue until age 6 months, after which infants will switch to a classical nontrial follow-up formula (not provided by the sponsor) until age 12 months. The study formulas will be provided in bottles of 70 mL stage 1 liquid ready-to-feed with each dispensing unit (carton) coded with a unique identifier and containing 32 bottles. The packaging and labeling of each bottle or carton will be identical for both groups, except for this unique identifier. The amount of formula offered to the infant will be informed by a physician or the recommended feeding table for this age group. Formulas will be consumed daily, ad libitum, per standard practice. The BG will continue exclusively breastfeeding at least until age 3 months and continue to breastfeed as per standard Chinese feeding recommendations up to study end.

Participants may be discontinued from the trial or the product if they withdraw consent to participate or from the trial product. This should have no impact on the participant and will be done without reprisal as per the Declaration of Helsinki. The investigator may also decide to discontinue a participant from the trial or the product if, in his or her opinion, continuation may be detrimental to the participant. Reason for discontinuation will be documented throughout the study.

### Study Outcomes

The primary end point of this trial will be *Bifidobacteria* abundance in fecal samples at age 3 months (before V2). *Bifidobacteria* play a central role in gut microbiome maturation at early stages of life. *Bifidobacteria* are the most predominant taxon during the first 6 months of life, hence we aimed to evaluate how the intervention will impact this taxon halfway through the period in which it is playing a key role in gut microbiome and immune maturation [35,36]. Secondary end points will include fecal microbiome and metabolic profile, fecal markers of immune health, gut barrier integrity and inflammation, gastrointestinal tolerance, immune competence, sleep quality, infant health-related quality of life, growth, infant feeding and dietary patterns, and AEs.

### Bifidobacteria Abundance

DNA will be extracted from the fecal samples, and microbiome composition will be assessed using next-generation sequencing (NGS) and quantitative polymerase chain reaction. The fecal sample collected at age 3 months (just before V2) will be used to examine the differences between intervention groups (EG and CG) in *Bifidobacteria* abundance, the primary end point.

### Secondary Fecal Outcomes

Fecal microbiome, including overall taxonomic and functional composition and diversity, will be assessed at all time points (V1 to V5) using NGS. The assessment includes a relative abundance of beneficial bacterial species (eg, *B infantis*), pathogenic bacterial species, α diversity, β diversity, fecal community types, and functional annotation of the collected samples. Fecal metabolic content will be measured by quantifying pH and organic acids (such as but not restricted to lactate (including indole-lactate, L- and D-lactate), propionate, butyrate, acetate, valerate, total organic acids, and total short-chain fatty acids), at all time points (V1-V5). These organic acids will be profiled using ultra-high performance liquid chromatography coupled to tandem mass spectrometry. Additionally, targeted or untargeted metabolomics will be performed using high-performance liquid chromatography on the same samples. Fecal markers of immune health (secretory immunoglobulin A), gut barrier integrity (α1-antitrypsin, calprotectin, and lipocalin-2), and inflammation (IL-1β, IFN-γ, and TNF-α) will be measured at V1, V2, and V3 and quantified using an enzyme-linked immunosorbent assay. All fecal metabolites and markers will be reported as per wet stool weight and per dry stool weight (dry stool weight will be calculated to normalize the data for analysis). Plans for collection, laboratory evaluation, and storage of fecal samples are described in further detail in Additional File S1 in Multimedia Appendix 1.

### Gastrointestinal Tolerance and Stooling Patterns

Gastrointestinal symptoms and related behaviors will be captured by the Infant Gastrointestinal Symptom Questionnaire-13 [37] at V1, V2, and V3. This is a validated, 13-item instrument of behaviors that the infant has experienced from the parent’s perspective, with 5 domains including stooling, flatulence, fussiness, crying, and vomiting. The possible range of scores for the composite index is 13-65, with lower scores indicating lower discomfort. Good tolerance, some gastrointestinal distress, and not well-tolerated are reflected by scores of 13-23, 23-30, and >30, respectively.

Stool patterns, including stool frequency, consistency, and difficulty in passing stool, will be collected using a 1-day retrospective diary at baseline (V1) and a 3-day prospective stool diary completed at home by the parents at V2 and V3. Stool frequency will be computed as the mean number of reported stools. Stool consistency will be validated using a 5-point stool scale: 1=watery, 2=runny, 3=mushy or soft, 4=firm, and 5=hard [38], and the mean scores will be calculated. Difficulty in passing stool will be calculated as the number of stools reported as difficult of the total number of stools.

### Immune Competence

The Pediatric Immune System Index is a short questionnaire developed internally for use in healthy infants to assess their overall state of the immune system and is assessed at V2 to V5. The questionnaire has 21 items across the 4 domains of gastrointestinal, upper respiratory tract infections, LRTI, and skin allergies, and records the duration, episodes, severity of health care visits, and treatment received for the most severe case. The responses recorded for each of the items are mapped to a score of 0, 1, 2, or 3. The final score (varying from 0 to 63) corresponding to a participant for a visit is then calculated as the sum of the individual item scores, with 0 indicating the best and 63 indicating the worst immune health.

### Sleep Quality

Sleep quality will be assessed at V1, V2, and V3 using the Brief Infant Sleep Questionnaire that has been validated against actigraphy and sleep diaries [39]. The Brief Infant Sleep Questionnaire is a 13-item parent-reported questionnaire on infant or toddler sleep over the past week, takes about 5-10 minutes to complete by the parent or caregiver, and assesses nocturnal sleep duration, night wakings, and method of falling asleep.

### Quality of Life

Infant quality of life will be measured at V2 and V3 using the Infant Toddler Quality of Life Questionnaire-Short Form 47, which has been validated in China [40,41]. It is a 47-item tool that asks about infant life across 9 domains: general health, physical functioning, growth and development, discomfort and pain, temperament and mood, behavior, social interaction, health perception, and anxiety and worry. Scores range from 0 to 100 for each domain, with 0 indicating the worst quality of life and 100 indicating the best quality of life.

### Growth

Anthropometric measurements, including weight (g), length (cm), and head circumference (cm), will be collected at all visits. Infants will be weighed without clothing or a diaper on a calibrated electronic weighing scale, and the weight will be recorded twice to the nearest 10 g. Using a standardized infant length board, length will be recorded twice to the nearest 0.1 cm with the infant looking vertically upward and the crown of the infant’s head in contact with the headpiece of the board. Infant head circumference will be measured twice to the nearest 0.1 cm using a standard nonelastic plastic-coated measuring tape. Sex- and age-specific *z* scores, including weight-for-age, weight-for-length, length-for-age, and head-circumference-for-age, will be calculated using the World Health Organization (WHO) Child Growth Standards as the reference population [42].

### Safety Reporting

Safety assessments will involve the monitoring and recording of all AEs and serious AEs throughout the trial upon signature of informed consent until the end of the trial or follow-up. Additional safety evaluations may be performed when medically indicated or in the opinion of the investigator. Parents or caregivers will be responsible for completing the infant illness diary (IID) weekly from enrollment until V5. The diary will ask the parent to capture the number of occurrences and the length of time the infant experiences the following symptoms: (1) fever, (2) respiratory tract symptoms, (3) gastrointestinal symptoms, (4) ear symptoms, as well as any medications the infant may be taking. The diary entries will be reviewed at each scheduled site visit or via regular phone calls, and the trial physician will validate the symptoms and associated diagnosis. Physical examinations will be performed at the baseline visit (V1) and the end (V5) or if deemed necessary at other visits for medically significant reasons. Details about the events including participant and date, description, reporting source, dispensed investigational product, duration, frequency, intensity (mild, moderate, or severe), seriousness, action taken, outcome, and sequelae if any, and relationship to test product (unrelated, unlikely, probable, or related), will be documented thoroughly.

### Additional Variables of Interest

#### Demographic Data, Birth, and Household Characteristics

Demographic data including age of child, sex, ethnicity, birth characteristics (birth weight and length, gestational age at birth, parity), APGAR (appearance, pulse, grimace, activity, and respiration) score at 5 minutes, feeding history (eg, breastmilk, formula, or complementary feedings), maternal age, education, health history and family history of allergy will be collected from the participant or parents or LARs at the enrollment visit (V1).

#### Feeding and Dietary Patterns

A 3-day food intake diary will be collected before each fecal sample is collected when the infants are aged 6, 9, and 12 months to evaluate the energy and nutrient intake, dietary pattern, and the introduction of complementary foods. Compliance with breastfeeding will be assessed among the BG infants using the breastfeeding diary, which will capture details about the frequency, duration, and type of breastfeeding (exclusive, predominant, or partial) at each visit (V1-V5). Additionally, parents or caregivers will complete the formula milk intake diary, which will collect information regarding the total quantity of milk consumed for each formula feeding from V1 to V5 in the EG and CG infants. These dietary and feeding-related data may be used as a covariate for the gut microbiome analysis, as gut composition is highly diet dependent.

#### Concomitant Treatments and Medications

Trial infants may receive any medically needed treatment, therapy, or medication, and there are no unauthorized treatments or medications. Parents or LARs will be requested not to give any prebiotic, or probiotic supplement from enrollment until after the stool sample is collected, just before V5 (age 12 months), unless medically prescribed or recommended by the infant’s physician. If given, prebiotic or probiotic supplements will be considered as concomitant medications and will be reported in the electronic case report form (eCRF) until V5.

#### Concomitant Diets

Introduction of complementary foods before V2 (infant age of 3 months) will be considered unauthorized per current recommendations for feeding healthy newborn infants and recorded as nontrial feeding in the eCRF. Additionally, any formula other than the trial formulas (CG and EG infants only) from the collection of the 1st stool sample (home [H1]) until intervention end (V3), and any infant formula in the BG before V2 will also be recorded as nontrial feeding in the eCRF. Finally, any prebiotic- or probiotic-containing foods until V2 will be reported as nontrial feeding in the eCRF for any of the groups.

### Data Analysis

#### Sample Size

The sample size was calculated based on the primary end point of the trial and an additional nonrandomized breastfed arm. To demonstrate a statistically significant increase of 8% in relative *Bifidobacteria* abundance at 3 months in the EG versus CG infants with a power of 80% and an α-level of 5%, a sample size of 105 per arm (including a 20% attrition rate) will be needed. For the nonrandomized breastfed reference arm, assuming a noninferiority margin of 20% in *Bifidobacteria* abundance with the experimental formula arm, the required sample size will be 52 infants (including a 20% dropout rate). Therefore, the total sample needed for this trial will be 262 infants (105 EG, 105 CG, and 52 BG).

#### Statistical Analysis

A staged statistical analysis (SSA) is defined as any statistical analysis performed when recruitment is completed, all participants have completed a predefined specific time point before the last participant last visit has been performed, and before the final database for the trial is locked.

The estimates computed at the SSA are considered final as all the participants have passed the predefined specific time point. The SSA will not lead to any modification in the design and subsequent conduct of the trial. Its sole purpose is to accelerate the availability of the key end point estimates. For this study, in addition to the final analysis, 2-stage statistical analyses are planned at 3- and 6-month visits. The analysis of the primary end point will be included in the first SSA.

Data will be analyzed on the following analysis populations:

Full analysis set (FAS): the FAS will exclude randomized participants who never took any of the assigned product (trial formula or breastmilk), participants who failed to satisfy trial entry eligibility criteria, or had no postrandomization data. This will be derived according to the assigned product group per randomization.Safety analysis set (SAF): the SAF will include all participants in the FAS dataset with documented use of at least one feeding of the trial formula or breastmilk for the BG, classified according to the feeding actually received, irrespective of the randomization assignment.Per protocol set (PPS): the PPS will include participants in the FAS with no major protocol deviations. Participants with major protocol deviations related to Good Clinical Practice (eg, ICF process not followed) will not be removed from PPS by default. A separate listing of these participants will be provided in the statistical report. The protocol deviations (eg, product compliance or visit window) will be defined before trial start. The listing of the protocol deviations will be reviewed during the blinded data review meeting.

The primary end point will be assessed on both FAS and PPS populations. All secondary end points will be analyzed on the FAS except for safety end points, which will be on the SAF. No interim analyses are planned for this study.

For all categorical and continuous variables, appropriate descriptive statistics will be calculated by visit, feeding groups, and delivery mode. The primary end point of the difference in *Bifidobacteria* abundance between EG and CG infants will be analyzed using analysis of covariance (ANCOVA), correcting for baseline, site, gender, and mode of delivery. If the investigation of data reveals an inflation of the null values (no detected *Bifidobacteria* in samples), then the ANCOVA model will be replaced by a 0-inflated mixture model. For continuous secondary end points, ANCOVA models correcting for baseline, site, gender, and delivery will be used for analyses. For categorical secondary end points, logistic regression models will be used to compare between feeding groups at each time point separately. Fecal metabolism and immune health markers will be analyzed according to dry stool weight, using an ANCOVA model at each time point to compare between feeding groups, correcting for baseline, site, gender, and mode of delivery. The necessity to log-transform the end points or to use nonparametric methods will be assessed during the blind data review and addressed in the statistical analysis plan. During the final analysis, the models may be modified to a mixed model repeated measurements to consider the longitudinal nature of the data. AEs will be compared between feeding groups using the Fisher exact test.

Missing data will be assumed to be missing at random unless the blind review of the data demonstrates a pattern of missingness, in which case, multiple imputation for the primary outcome of *Bifidobacteria* abundance at 3 months may be used. In the case of outliers for any end point, robust approaches or sensitivity analyses may be used. Statistical testing for all end points will be 2-sided and at a 5% significance level. All statistical analyses will be performed in SAS Life Science Analytics Framework (version 5.4.1; SAS Institute Inc).

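### The safety set is restricted to the full analysis set, so infants fed trial formula but later found ineligible drop out of the safety analyses

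*Protocol article*

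**What the plan says.** Three statements in the Statistical Analysis section of the protocol article fix the safety population.

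- **FAS.** "the FAS will exclude randomized participants who never took any of the assigned product (trial formula or breastmilk"; the same sentence also excludes "participants who failed to satisfy trial entry eligibility criteria, or had no postrandomization data".
- **SAF.** "the SAF will include all participants in the FAS dataset with documented use of at least one feeding of the trial formula" (breastmilk for the breastfed group), and these infants are "classified according to the feeding actually received, irrespective of the randomization assignment".
- **Use.** Secondary end points are analysed on the FAS, "except for safety end points, which will be on the SAF".

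The same section adds that "AEs will be compared between feeding groups using the Fisher exact test". The Safety Reporting section commits to "monitoring and recording of all AEs and serious AEs throughout the trial upon signature of informed consent until the end of the trial" or follow-up. The article describes no other safety population. The one separate participant listing it names concerns Good Clinical Practice deviations and relates to the per protocol set.

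**The concern.** A safety population should contain everyone exposed, because its purpose is to describe what happened after exposure. Here it inherits every FAS exclusion, and those exclusions have reasons other than non-exposure. Failing an entry criterion does not undo a feeding that has already taken place.

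At stake are the completeness of the adverse event tables and of the between-group comparison. An infant who was fed trial formula, had an event, and was then found ineligible would have that event recorded but not analysed. Some entry criteria concern tolerance of the formula base. One excludes "Infants with a known or suspected cow’s milk protein intolerance or allergy, lactose intolerance", and both formulas are based on bovine milk. An ineligible but fed infant can therefore be one whose outcome a safety reader would want to see, though this need not be so.

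There is also an internal tension. The SAF is meant to group infants by what they were fed, whatever their assignment. If assigned product means the formula of the infant's own arm, an infant fed only the other formula is removed at the FAS stage, and the as-fed rule never reaches the clearest case it was written for.

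**Working it through.** The article states no figure that this point depends on, so there is none to reproduce. The check is of set membership, followed by a scale calculation.

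**1. The rules as written (Statistical Analysis section)**

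- FAS = took some assigned product AND met entry criteria AND has data after randomization.
- SAF = FAS AND one or more documented feedings.
- An exposure-based safety set = one or more documented feedings.

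**2. All exposed cases, strict reading**

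For a randomized infant with at least one feeding there are 2 (eligible or not) × 3 (assigned formula only, both formulas, other formula only) × 2 (later data or none) = 12 logical combinations. These are types of case, not numbers of infants.

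| Eligible | Formula taken | Later data | In SAF as written | In exposure-based set |
|---|---|---|---|---|
| yes | assigned only | yes | yes | yes |
| yes | both | yes | yes | yes |
| yes | other only | yes | no | yes |
| yes | any of the three | no | no (3 cases) | yes (3 cases) |
| no | any of the three | yes or no | no (6 cases) | yes (6 cases) |

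As written, 2 of 12 enter. With exposure alone, 12 of 12 enter.

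**3. The same cases, most lenient reading**

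Suppose assigned product means the feeding type, so that either trial formula counts. Suppose also that a documented feeding after randomization is itself later data. The cases with no later data then disappear, leaving 2 × 3 = 6. All 3 eligible cases enter the SAF. All 3 ineligible cases stay out.

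The loss of ineligible but fed infants therefore survives every reading. The wrong-formula loss depends on the strict reading, and even then covers only infants who took none of their own arm's formula. The no-data loss largely disappears once a feeding or an adverse event is accepted as data.

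**4. Scale**

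- Planned size per formula arm (Sample Size section): 105, so 2 × 105 = 210 randomized.
- One infant as a share of an arm: 1/105 = 0.95%.
- The article gives no rate of ineligible but fed infants. As a pure assumption, 1% to 5% of 210 gives 210 × 0.01 = 2.1 to 210 × 0.05 = 10.5, or about 2 to 11 infants.

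**5. Direction**

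Take an arm with one infant who has a given event: 1/105 = 0.95%. If the omitted infant is that one, the observed rate becomes 0/104 = 0%. If the omitted infant had no event, it becomes 1/104 = 0.96%. The number of infants with events can only stay the same or fall, but the rate can move either way, and so can the difference between arms.

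**The case against.** The strongest reply accepts that the SAF is nested in the FAS but holds that little follows from it. Its parts differ in weight.

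- **Wrong product.** A reader might infer that every infant given the wrong product is lost. The text does not support this. The FAS sentence glosses assigned product by feeding type, and it mentions breastmilk although breastfed infants are not randomized. Read that way, an infant fed the other arm's formula stays in and the as-fed rule works. Even on the strict reading, an infant who took some of both formulas stays in. What stands is an ambiguity to remove.
- **No later data.** A reader might infer that infants with no later data take hidden events with them. Randomization is at the first visit and formula starts after the baseline stool, so a feeding or an event on formula is arguably data after randomization. An infant with truly none has no on-formula event to lose.
- **Highest-risk infants.** A reader might infer that the infants removed are those most likely to react to formula. Many criteria have no evident link to a reaction: birth weight, age window, singleton birth, access to a freezer, participation in another trial. The allergy criterion concerns what was known or suspected at entry, and formula-fed infants must already have tolerated a cow's milk formula for at least 3 days. An infant whose allergy first appears on trial formula did not fail entry and remains in both sets.
- **Understated rates.** A reader might infer that adverse event rates are biased downward. The direction is unknown, as shown above, and under blinding nothing points to a difference between arms.
- **Conflict with Safety Reporting.** That section governs what is recorded, and the analysis-set definitions govern what is analysed. The two do not contradict each other. The events are collected and may appear in listings that a condensed article does not describe.
- **Rarity.** Eligibility is checked at the first visit, so late discoveries should be few. This limits the size but does not justify the rule.

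None of this reaches the ineligible but fed infant, who is excluded on any reading.

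**Conclusion.** Wrong as written. The SAF definition carries the FAS eligibility exclusion into the safety analysis, so infants who were fed trial formula and later found ineligible are left out of the safety end point analyses and the Fisher comparisons, although their events are recorded. This is a stated rule, not a detail left for the analysis plan. The possible loss of infants fed only the other arm's formula is secondary and depends on how assigned product is read.

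The size is unknown. Each omitted infant is about 1% of an arm, and the range of about 2 to 11 infants rests wholly on the assumed 1% to 5%. The documents do not support a claim that adverse event rates would be understated or that the infants at greatest risk are the ones lost. The primary end point is unaffected, since it is analysed on the FAS and per protocol set.

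**What to change.** Delete the restriction to the FAS from the SAF definition. Define the SAF as all enrolled infants with one or more documented feedings of either trial formula (or of breastmilk, for the breastfed group), classified by what they were actually fed, whether or not they belong to the FAS. In the FAS sentence, state whether assigned product means the formula of the infant's own arm or any trial formula.

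The cost is a sentence or two in the protocol and the matching text of the analysis plan. No new data, visits or sample size are needed, because adverse events are already recorded from consent. Make the change while the trial is blinded and before the first staged analysis, whose estimates the article treats as final. Staged analyses follow completed recruitment, and the article's June 2025 status was 122 recruited of a planned 262, so at that date the change could still have been made in time.
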